#### SECONDARY ANALYSES

Secondary outcomes measured once before, during, and after treatment will be analyzed in a similar fashion as for the primary outcome, modelled after data's distribution (count or continuous). Measures collected only once at baseline and post-treatment will be analyzed with regression analyses including treatment group (online ERITA , TAU) as the between-subjects factor, time (baseline to post) as the within-subjects factor, and group  $\times$  time interactions, modelled after data's distribution (count or continuous).

Parallel process latent growth curve modeling will be used to determine whether change in week-to-week emotion dysregulation (DERS-16) during treatment mediate the overall effect of ERITA+ETAU on week-to-week change in the primary outcome self-rated NSSI frequency (DSHI-Y).

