## POWER

The sample size of this study was determined based on the observed treatment effects in the uncontrolled pilot study of iERITA (EPN: dnr 2015/1895-31/5). Based on an expected average difference of two self-harming episodes between the groups at post-treatment yields a total sample size of 140 participants with a power of 82% given alpha .05, after the 12-week follow-up. Given an estimated attrition rate of 15%, we aim to include 165 adolescents.

The power refers to a 0.05-level Wald test for the interaction between a binary treatment and linear time in a zero-inflated negative binomial regression model at a 0.05 level. The power was estimated with 200 bootstrap samples. The data for the treated group were obtained by sampling with replacement from the available pilot data. The data for the control group was obtained by adding the difference to the count of a bootstrap sample from the iERITA pilot data on the 25 treated patients.

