If the adolescent and parent(s) consent to participation, they will receive information on how to log on to a secure website comprising pre-assessment and information on demographic variables for both the adolescent and his/her parents. Once the pre-assessment is completed, randomization is executed. The family could either be allocated to starting treatment immediately or start treatment 24 weeks later (when the intervention group has completed the three month follow-up). The treatment lasts for twelve weeks. Both groups are asked to undergo the post-assessment approximately twelve weeks after the pre-assessment. The post-assessment could either be done face-to-face, or via telephone. The follow-up measures at three, six, and twelve months are done via the phone. All assessments are done by the treating clinician (psychologists, psychologists under training or psychotherapists); the post- and follow-up measures are conducted by independent assessors.

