#### PRE-, POST AND FOLLOW-UP ASSESSMENTS FOR THE ADOLESCENTS

The pre- and post-assessments includes the structured clinician administrated assessment of the adolescent's functional impairment (CGAS), NSSI (CANDI and DSHI-Y), emotion dysregulation (DERS and DERS-16), borderline personality disorder symptomatology (BPFS-C) and other self-destructive behaviors (BSL-Supl), suicidal ideation (SIQ-JR), accepting stance (AAQ-2), depression, anxiety and stress (DASS-21), and client satisfaction (CSQ). At post and follow-up assessments questions regarding potential adverse events will be addressed (Adverse events). In addition to these scales the therapist will rate participant adherence during treatment (iiPAS).

Weekly measures will be administered four weeks before the face-to-face assessment, during treatment, and four weeks after treatment termination. Four weekly measures will also be administered at each follow-up. The weekly measures consist of four short self-report scales that measure emotion regulation (DERS-16), NSSI (DSHI-Y), other self-destructive behaviors (BSL-Supl), and attachment (ECR-RC). In addition to these scales the participant will be asked to report if there have been any changes in medication during the past week. At treatment week 1, treatment expectancy/credibility (CEQ) will be rated, and therapeutic alliance (WAI) will be rated at week 4. The participants will answer a maximum of 58 questions per week. For a measurement chart, see figure 1.

323

[figure not shown]

324

325 *Figure 1. Chart over the different assessments and measures for both the intervention and waitlist*  
326 *group.*

327

328 PRE-, POST- AND FOLLOW-UP ASSESSMENTS FOR THE PARENTS

329 Parents will complete questionnaires about their own possible history of NSSI (SITBI-SF-SH), and  
330 about how they cope with their child's negative emotions (CCNES-A). At post, questions regarding  
331 potential adverse events will be addressed (Adverse events).

332 PRELIMINARY RESULTS

333 As a first step in evaluating the feasibility, acceptability, and utility iERITA for adolescents with  
334 repeated NSSI, the research group has conducted an open pilot study including 25 adolescents with  
335 NSSID, aged 13-17 years (EPN dnr 2015/1895-31/5). To date, all adolescents have completed  
336 treatment, 24 participants have provided post-treatment data and so far, 19, and 15 participants,

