#### PRIMARY ANALYSIS

The primary outcome analysis will include treatment group (ERITA , TAU) and weekly reports of NSSI frequency measured once every week 4 weeks prior to treatment start, once every week during treatment, and once every week four weeks after treatment termination. Regression analysis modelled for count data will be used to estimate trend over time. Four weeks after treatment termination will be considered primary endpoint. Pairwise contrasts (group x time interaction) from the regression model will be used to evaluate between-group differences at primary endpoint (4 weeks after treatment termination).

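### Secondary outcomes measured only at baseline and post-treatment are tested by group × time with a free baseline difference: valid, but less precise than an analysis that uses the pre-randomisation baseline

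*Protocol*

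**What the plan says.** The Protocol, Secondary Analyses, names the terms of the model for two-wave outcomes: "Measures collected only once at baseline and post-treatment will be analyzed with regression analyses including treatment group" "as the between-subjects factor, time (baseline to post) as the within-subjects factor, and group" by time interactions, with the error distribution "modelled after data's distribution (count or continuous"). The baseline value is thus one of two responses, group is an unconstrained main effect, and the treatment effect is the interaction. No baseline covariate or common baseline mean is mentioned anywhere under Statistical Analyses.

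On timing, Procedure states: "Once the pre-assessment is completed, randomization is executed".

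On the outcomes, the section on assessments for the adolescents states: "The pre- and post-assessments includes the structured clinician administrated assessment of the adolescent's functional impairment (CGAS"), and goes on to emotion dysregulation, borderline features, suicidal ideation, acceptance, and depression, anxiety and stress. Some scales (DSHI-Y, DERS-16, BSL-Supplement, ECR-RC) are also weekly, so they are not two-wave measures. The parents' coping scale has its own pre-, post- and follow-up section.

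The Power section concerns NSSI counts only. It gives no SD, baseline–post correlation or power for any two-wave outcome.

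**The concern.** Because everyone is assessed before allocation, the true baseline difference between arms is zero. The planned model nevertheless estimates that difference freely and subtracts it in full from the difference at post. When baseline and post are imperfectly correlated, subtracting the whole baseline difference overcorrects and adds noise. Using baseline as a covariate, or giving the arms one baseline mean, removes only the part that predicts the post value.

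What is at stake is power and interval width on the two-wave secondary outcomes. The trial was not sized for these, and about 140 participants are expected to be analysable.

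**Working it through.** **Inputs.** 70 per group, 140 in total, and 15% attrition (Protocol, Power, and the table in the power appendix). Baseline before randomisation (Procedure). Model terms (Secondary Analyses). Assumptions, because the protocol is silent: ρ from 0.3 to 0.9, equal SDs at the two visits (set to 1), and a two-sided 5% test.

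**The plan's own figure.** 140/(1 − 0.15) = 164.7, so 165, as stated. The 82% power comes from resampling pilot counts that are not in the document, so it cannot be recomputed, and it is not needed here.

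**Step 1: what the interaction estimates.** With two visits and complete continuous data, the group × time coefficient is (treated post − treated baseline) − (control post − control baseline), the difference in mean change. In one simulated data set (70 per arm, ρ = 0.5), the mixed-model interaction and the change-score difference were both −0.6106 (SE 0.1558). The baseline-adjusted estimate was −0.6175 (SE 0.1423).

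**Step 2: variances, with n per arm and SD 1.**
- Interaction: (2/n) × 2(1 − ρ)
- Baseline-adjusted: (2/n) × (1 − ρ²)
- Ratio, adjusted to interaction: (1 − ρ²)/[2(1 − ρ)] = (1 + ρ)/2

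At ρ = 0.5 the SEs are √(2/70 × 1.00) = 0.169 and √(2/70 × 0.75) = 0.146. The ratio is √0.75 = 0.866, a fall of 13%.

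If the SDs differ (s₀ at baseline, s₁ at post), the interaction variance exceeds the adjusted one by a term proportional to (s₀² + s₁² − 2ρs₀s₁) − s₁²(1 − ρ²) = (s₀ − ρs₁)². This is never negative, so in large samples adjustment is not less precise.

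**Step 3: results at 70 per arm.** Each pair is interaction, then baseline-adjusted. The detectable difference is (1.960 + 0.842) × SE, for 80% power. The 0.4 SD effect is illustrative.

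| ρ | SE | Fall in SE | Detectable difference (SD) | Power at 0.4 SD |
|---|---|---|---|---|
| 0.3 | 0.200, 0.161 | 19% | 0.56, 0.45 | 52%, 70% |
| 0.5 | 0.169, 0.146 | 13% | 0.47, 0.41 | 66%, 78% |
| 0.7 | 0.131, 0.121 | 8% | 0.37, 0.34 | 86%, 91% |
| 0.9 | 0.076, 0.074 | 2.5% | 0.212, 0.206 | about 100% for both |

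**Step 4: simulation.** Over 4000 simulated trials per ρ with a true effect of 0.40, the average estimates lay between 0.400 and 0.407 for both methods. The ratios of empirical SEs were 0.82, 0.86, 0.92 and 0.98 at ρ = 0.3, 0.5, 0.7 and 0.9.

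**Step 5: missing post values.** Suppose the planned model is fitted by likelihood and keeps dropouts' baselines, with N = 165/2 = 82.5 baselines and m = 70 post values per arm. The interaction variance per arm is then (1 − ρ²)/m + (1 − ρ)²/N, against (1 − ρ²)/m after adjustment. At ρ = 0.5 that is 0.75/70 + 0.25/82.5 = 0.01374 against 0.01071, an SE ratio of 0.88. At ρ = 0.3, 0.7 and 0.9 the ratios are 0.83, 0.93 and 0.98.

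**Step 6: counts.** Here the interaction is a ratio of rate ratios, the log-scale analogue of a change comparison. In 600 simulated trials per setting (overdispersed Poisson counts, rate ratio 0.65, latent correlation 0.5 or 0.8), adjusting for log baseline gave nearly the same mean effect, with SE ratios of 0.84 to 0.93. Zero-inflated models were not examined.

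**The case against.** The strongest reply is that nothing here is wrong: the planned test is unbiased, keeps its type I error, and loses only power on secondary outcomes. The Secondary Analyses section is brief, and an analysis plan that was not available might add covariates. The first part stands and limits the weight of the point. The second does not remove it, because the protocol itself names the model terms and the contrast.

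Two further replies stand. The gain depends on ρ, which the protocol does not give, and it is negligible near 0.9. A plain covariate analysis also leaves out participants without a post value, whereas a likelihood repeated-measures model with the planned terms would keep them. The constrained model keeps them too, so retention is an advantage over the simple covariate analysis and not over the planned model.

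A reader might infer several stronger points that the documents do not support:
- **That the primary analysis has the same defect.** It also uses a group × time contrast: "Pairwise contrasts (group x time interaction) from the regression model will be used to evaluate between-group differences at primary endpoint". But it is a count trend model with four weekly baseline reports, weekly reports during treatment and four afterwards. The two-wave formula does not apply, and no gain was computed for that design. The power calculation also rests on an interaction: "The power refers to a 0.05-level Wald test for the interaction between a binary treatment and linear time".
- **That every scale at the pre- and post-assessments is affected.** The measurement chart is not shown, and follow-up assessments are planned, so which scales count as two-wave cannot be confirmed.
- **That both analyses give the same answer.** They share an expectation. In one trial the estimates differ, by 0.07 SD on average at ρ = 0.5.
- **That chance baseline imbalance is a second harm.** Averaged over randomisation, it is the excess variance already counted.

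**Conclusion.** The point holds for secondary outcomes collected only at baseline and post-treatment. The planned interaction test is valid but avoidably imprecise. Baseline adjustment targets the same effect with (1 + ρ)/2 of the variance, which means an SE smaller by about 19%, 13%, 8% and 2.5% at ρ = 0.3, 0.5, 0.7 and 0.9. With 15% missing post values the saving is a little smaller: about 17%, 12%, 7% and 2%.

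These figures assume equal SDs and a ρ that the protocol does not supply. The algebra is exact for continuous outcomes; for counts the support is an analogue checked by simulation only. Neither the sample size ("yields a total sample size of 140 participants with a power of 82% given alpha .05") nor the type I error is affected, and no claim is made about the primary NSSI model.

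**What to change.** In Secondary Analyses, for outcomes with one baseline and one post value, replace the interaction test by one of the following, with the same distribution family as now planned:

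1. **Preferred:** a likelihood-based longitudinal model with the baseline mean constrained equal in both arms. Drop the group main effect and keep time and the treatment effect at post. For continuous outcomes, leave the two variances and the correlation free. Participants without a post value stay in the model.
2. **Alternative:** the group effect at post, with the baseline value as covariate (log baseline for counts). State how participants without a post value are handled, so that this fits the intention-to-treat principle the protocol adopts.

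List the outcomes treated as two-wave, and justify the common baseline by the order given under Procedure. The cost is a change of wording and at most about one degree of freedom. No new data are needed, and the sample size and primary analysis stay as they are.

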#### AIMS AND OBJECTIVES

The overall objective of the present study is to evaluate the efficacy of adding iERITA to treatment as usual (TAU), compared to treatment as usual only. Further objectives are to investigate the possible mechanisms of change, prognostic factors, and to evaluate the cost-effectiveness of the treatment. These are the specific research questions:

- Is participation in iERITA in addition to treatment as usual, more effective than treatment as usual only, in regards to reducing NSSI, other self-destructive behaviors, emotion dysregulation, acceptance, suicidal thoughts and behaviors, depression, stress, and anxiety, for adolescents with repeated NSSI?
- Is participation in the parent program in addition to treatment as usual, more effective than treatment as usual only, in regards to enhancing the parent's perceived ability to cope with their child's negative emotions?
- Is iERITA associated with improved emotion regulation and attachment? If so, does improved emotion regulation mediate treatment outcome, and is attachment a potential competing mediator?
- Is it possible to identify predictive factors (e.g. age, NSSI frequency, BPD-symptoms, childhood trauma and psychiatric comorbidity) for treatment outcome?

- Can iERITA imply economic advantages?
- In which context (i.e. circumstances, antecedents, and consequences) does NSSI occur in, when reported in real time?

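### The one mediation analysis named uses DERS-16 alone, with no lag or reverse path, so it neither addresses attachment as a competing mediator nor shows the direction of effect

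*Protocol*

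**What the plan says.** Under Aims and Objectives the protocol asks whether iERITA improves emotion regulation and attachment and, if so, "does improved emotion regulation mediate treatment outcome, and is attachment a potential competing mediator".

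Secondary Analyses names one mediation analysis, a parallel process growth model to "determine whether change in week-to-week emotion dysregulation (DERS-16) during treatment mediate the overall effect of ERITA+ETAU on week-to-week change in the primary outcome", which is DSHI-Y frequency. The qualifier about the treatment period is attached to DERS-16. The NSSI window is not given separately. Under Primary Analysis, the weekly NSSI series is collected in the four weeks before treatment, then "once every week during treatment, and once every week four weeks after treatment termination".

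The section on adolescent assessments lists the four weekly scales: "emotion regulation (DERS-16), NSSI (DSHI-Y), other self-destructive behaviors (BSL-Supl), and attachment (ECR-RC"). On timing it says: "Weekly measures will be administered four weeks before the face-to-face assessment, during treatment, and four weeks after treatment termination". Attachment is also listed among the secondary outcome measures, so the general rule for secondary outcomes covers the treatment effect on attachment. No part of Statistical Analyses gives attachment a role as a mediator.

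**The concern.** There are two difficulties, and both come from what the protocol names.

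First, the aim poses a question about two candidate mediators and the named analysis contains one. If attachment change drives both DERS-16 and NSSI, a DERS-16-only model can credit emotion regulation with an effect that it does not have.

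Second, randomisation protects the path from treatment to mediator. It does not protect the path from mediator to outcome. When both are slopes estimated from overlapping weekly series, better emotion regulation leading to less self-harm and less self-harm leading to better emotion regulation give the same data pattern.

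At stake is the mechanism claim. The protocol's background reports that emotion-regulation change mediated NSSI improvement in the 17-person face-to-face pilot. This larger randomised trial, with weekly measurement, could test that claim harder than the named model does.

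**Working it through.** The protocol gives no figure for the mediation analysis, so there is none to reproduce. The illustrations take only the sample size from it: the Power section "yields a total sample size of 140 participants with a power of 82% given alpha .05". As a side check, 140 / (1 − 0.15) = 164.7, which rounds up to the stated target of 165.

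**1. Aim against analysis.** The aim names emotion regulation and attachment as mediators. The weekly data contain both. The analysis names only emotion regulation (DERS-16).

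**2. Equal fit in either direction.** Let X be treatment, M the DERS-16 slope and Y the NSSI slope. The forward model is f(M | X) · f(Y | M, X) and the reverse is f(Y | X) · f(M | Y, X). Both equal f(M, Y | X). In linear normal form each has 3 + 4 = 7 parameters: intercept, treatment path and variance for the first equation; intercept, treatment path, cross path and variance for the second. The joint distribution also has 7: two means in each of two arms, plus two variances and one covariance. Both models are therefore saturated and have the same maximum likelihood. In 2,000 simulated trials per scenario the largest log-likelihood difference was about 1e-13, which is rounding error. The result requires the direct treatment path to be in the model. Without it the two models can differ, but only through an assumption of full mediation.

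**3. Apparent mediation when the true share is zero.** Take slopes standardised within arm, with Y = cX + e and M = rY + u, and no effect of M on Y. Then a = rc, b = cov(Y, M | X) / var(M | X) = r, indirect effect = r²c and total effect = c. The apparent share mediated is r²: 0.5² = 25% or 0.7² = 49%. Both values of r are assumptions.

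**4. How often it would be declared.** The simulation used 140 participants allocated 1:1, 12 concurrent weekly measures, per-person slopes, a direct path, and a joint-significance test at 1.96. It approximates the planned model in two stages with normal data.

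| Assumed truth | DERS-16 mediation declared | Reverse mediation declared |
|---|---|---|
| DERS-16 drives NSSI (paths 0.5) | 71.2% | 20.6% |
| NSSI drives DERS-16 (paths 0.5) | 21.5% | 68.1% |
| Attachment drives both (paths 0.6, 0.5, 0.5) | 13.2% | 11.7% |

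In the third row DERS-16 has no effect on NSSI. Adding the attachment slope reduced the false declaration from 13.2% to 2.5%. The Monte Carlo standard error at 21.5% is √(0.215 × 0.785 / 2000) = 0.9 points.

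**5. A repair that does not settle direction.** One might use the DERS-16 slope in weeks 1–6 to predict NSSI in weeks 7–16. In simulation with no DERS-16 effect on NSSI (assumed effects 0.5, N = 140), that path was falsely significant in about 66% of trials, and in 68% after adjusting for early NSSI. The spurious share mediated fell from about 19% in the concurrent model to about 6% and 3%. The bias shrinks, but the test still does not identify direction.

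**The case against.** The strongest reply is that the statistical section is a summary. It also names no analysis for predictors of outcome, cost-effectiveness or the context of NSSI. A statistical analysis plan, not seen here, may add attachment and lagged models. The aim itself is conditional and speaks only of a potential competitor. Parallel process growth modelling is also a recognised method for this kind of question. This stands in part: a reader might infer that the competing-mediator question will go unanswered, but the protocol shows only that the analysis it names does not address it. The reply does not remove the point, because here the protocol fixes the model, the mediator and the outcome, and the result does not match its own aim.

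Two further inferences go too far. One is that the model merely correlates two slopes over identical weeks. Such models normally regress the outcome slope on the mediator slope, and the NSSI window is not stated separately and may run four weeks past treatment. The series would still overlap with no lag. The other is that 25% or 49% of the reported effect would be spurious. Those shares rest on assumed correlations and on pure reverse causation.

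It could also be said that the table shows some information on direction, since the true direction is declared more often. That gap comes from the assumed sizes of the treatment effect on each slope. The fit of the two models remains identical.

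**Conclusion.** The point holds as a mismatch between aim and analysis and as a limit on interpretation. The named model has one mediator where the aim has two, and its mediator-to-outcome path fits equally well in reverse. The equal fit follows algebraically, given overlapping slopes and a direct treatment path. The false-declaration rates of 21.5% and 13.2% show that the problem can matter at this sample size, but they depend on assumed effects and a simplified two-stage normal model, and they do not predict this trial's result. The documents do not support saying that a mediation finding here would be wrong, only that it would not by itself establish that emotion regulation drove NSSI change. This concerns a secondary mechanism aim.

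**What to change.** In Secondary Analyses:

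- Enter ECR-RC as a second mediator alongside DERS-16 in the same model.
- State the weeks that define the mediator process and those that define the NSSI process.
- Add a lagged weekly model: DERS-16 and ECR-RC at week t predicting NSSI at week t+1, adjusted for prior NSSI and separating stable between-person differences from within-person change. Fit the reverse path (NSSI at week t to the mediators at week t+1) as a check.
- Keep the concurrent growth model, but report it as associational.

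An early-slope, later-outcome split should not stand in for the lagged model as a test of direction, for the reason shown in step 5 of the working.

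The cost is additional analysis and wider intervals on the indirect effects; no new data are needed. Lagging strengthens a claim about direction without proving it, because the mediators are not randomised and unmeasured confounding remains possible. If the sponsor prefers not to add these models, the alternative is to narrow the aim to what the concurrent DERS-16 model can describe.
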